### Trial organisation and administration

The SABRTooth trial is funded by the National Institute for Health Research (NIHR), Research for Patient Benefit (RfPB) Programme (PB-PG-0613-31114), and is sponsored by Leeds Teaching Hospitals NHS Trust.

Trial supervision will be established according to the principles of Good Clinical Practice (GCP) and in line with the relevant Research Governance Framework within the UK and through adherence with CTRU standard operating procedures (SOP). A core internal project team, TMG and TSC will be established, with the TSC performing a dual role and acting as the data monitoring and ethics committee (DMEC). Overall data and trial management will be provided by the Clinical Trials Research Unit (CTRU) (University of Leeds, UK).

### Qualitative interviews

The trial includes embedded qualitative exploration of the reasons for non-participation in the SABRTooth study. As the two treatments are very different, patients may have a strong preference for either surgery or SABR or may feel uncomfortable to have a decision between such different treatment options being taken out of their hands. What patients understand, perceive and feel about how the SABRTooth study and how it was presented to them and their expectations of study burden will be explored in qualitative feedback interviews. Participants who agree to participate in the study but subsequently do not take up their treatment allocation after being randomised will also be invited to take part in a feedback interview (Fig. 1). Understanding why patients choose not to participate or do not take up their treatment allocation will be crucial in assisting optimal recruitment methods and ensuring the most appropriate design of any subsequent phase III study.

#### Quality of life

Participants will be asked to complete questionnaires at baseline, day 1 of treatment, 6 weeks post-treatment and then 3 monthly until 24 months post-treatment or until the end of the trial follow-up period (6 months after the last patient has been randomised). Questionnaires to be completed include the following:EQ-5D™ and EQ-VAS™EORTC QLQ-C30 and QLQ-LC13 (not collected at 15- and 21-month time points)Baseline and follow-up resource use and societal–economic questionnaires

Questionnaires will be completed by participants at their standard clinic visits, i.e. baseline; day 1 of treatment; 6 weeks post-treatment; and 3, 6, 9, 12, 18 and 24 months post-treatment. Questionnaires due to be completed at 15 and 21 months post-treatment will be administered via post.

The frequent collection of quality of life (QoL) data within this feasibility study is necessary in order to assess the burden to patients. This will be assessed by monitoring compliance rates in terms of proportion of questionnaires returned and completed and will inform the optimal frequency of data collection for the planned subsequent phase III trial. Averaged QALYs are intended as a co-primary endpoint for the planned phase III trial, as such, determining the optimal frequency of EQ-5D data collection within this feasibility study is crucial. Utility estimates will be derived from the EQ-5D data collected within this feasibility study and used to inform the power calculations for the QALY co-primary endpoint.

### Health economics

As this is a feasibility study, a formal cost analysis or cost-effectiveness analysis will not be performed. The resource use and societal–economic data will be analysed and reported using descriptive statistics of frequency and quantity of specific resources used on average by patients. The objective will be to identify the main drivers of difference in resource use and out-of-pocket expenses between the two arms. Compliance and missing data will also be described. These data will inform an efficient design of the patient questionnaires in the subsequent phase III study.

### Statistical methods and analysis

Statistical analysis will be the responsibility of the SABRTooth CTRU trial statistician. A full statistical analysis plan will be written before any formal analyses are undertaken. As this is a feasibility study looking at recruitment potential, the analysis will be performed through descriptive statistics rather than formal hypothesis testing.

The analysis of the primary endpoint and all secondary endpoints relating to recruitment and withdrawals from the trial will take place at the end of the 21-month recruitment period. Final analysis of all other endpoint data will be carried out 6 months after the final participant has been randomised.

The primary endpoint analysis will be based on the population of participants recruited within the formal monitoring period. All further analysis will be carried out on the intention-to-treat (ITT) population defined as all participants randomised to the trial, regardless of adherence to the protocol, withdrawal of consent or losses to follow-up. Participants will be included within the treatment arm to which they were randomised.

An interim analysis will take place approximately midway through the study and be reported to the TSC. The aim of the interim analysis is to evaluate and monitor the key study objectives (i.e. recruitment rates, number of participants taking up their treatment allocation, feedback from the qualitative interviews), as well as expected serious complications (SCs) and unexpected serious complications (USCs) and the delivery time of surgery/SABR post-randomisation. The TSC will have the opportunity to raise any concerns with the trial progression/running allowing the trial team to improve processes going forward.

#### Primary endpoint analysis

Recruitment rates over the whole 21-month recruitment period will be reported overall and by recruiting site. The average recruitment rate per month and in total over the formal monitoring period will be reported in order to evaluate the primary objective of the study.

#### Secondary endpoint analysis

The total number of patients considered for the trial and assessed as being eligible will be reported by recruiting site along with reasons for non-randomisation.The proportion of participants undergoing their allocated treatment procedure (surgery/SABR) will be summarised overall, by treatment arm and by recruiting site, along with reasons for non-compliance.The proportion of QoL questionnaires returned and completed at each data collection timepoint will be reported overall, by treatment arm and by recruiting site. EQ-5D utility scores and standard deviations will be derived for each participant in line with the EQ-5D user guide. Average utility scores over follow-up will be presented for each treatment arm and overall and used to inform the sample size calculations for the planned phase III trial.

#### Exploratory data analysis

The feedback interviews will be professionally transcribed verbatim and managed with help of NVivo. The data will be analysed using inductive thematic analysis [18, 19]. The analysis will be further refined by using a constant comparison and contrastive approach and looking for negative cases in order to examine for similarities and differences within and between the patients in different sites and within and between patient groups.Descriptive summaries of the participant recruitment pathways at the individual sites and site criteria for identifying patients at a higher risk from surgical resection will be reported. Intended pathways and criteria used at the start of recruitment and subsequent changes during recruitment will be described.The 30-, 90- and 180-day mortality rates overall and in each treatment arm (measured post-treatment) will be summarised, and 95 % confidence intervals will be constructed. Given that these rates will be based on a limited sample, they will be treated as exploratory and used only to compare with recent figures in the literature rather than influence the sample size for the planned phase III trial.OS rates as obtained via the NCDR will be reported but an analysis formally comparing the two treatment arms will not be performed due to the lack of power within this feasibility study. By collecting OS data on all participants within this study, this may then be used in conjunction with the OS data generated from the planned phase III trial in a formal meta-analysis which will add to the overall evidence base for these two interventions.Rates of related complications, serious complications and unexpected serious compliances will be reported by treatment arm and overall, along with the average and range of delivery times of surgery and SABR post-randomisation.

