### Trial design

SABRTooth is a UK-based, multi-centre, open-label, two-group individually randomised controlled feasibility study targeted at patients with peripheral stage I NSCLC considered at higher risk from surgical resection. Patients will be randomised (1:1) to either SABR or surgical resection (Fig. 1). Due to the different treatment modalities, it is not possible to blind patients or clinicians to treatment allocation.

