### Trial population

Those patients considered at higher risk of complications from surgical resection are defined as “a level of fitness that could lead to a greater than average morbidity or mortality from surgery”. This includes those patients with poor lung function who are at risk of increased post-operative dyspnoea that would be sufficient to be unacceptable to them (this is subjective and will vary from patient to patient) and patients who have an increased risk of cardiovascular morbidity that might lead to a perioperative complication or death.

In order to maximise recruitment, the protocol does not specify what constitutes high risk but leaves it to the judgment of the individual MDT. However, we have produced guidelines (Fig. 1: SABRTooth trial schema; Table 1) to ensure appropriate patients are considered for the trial. We also intend to collect data on the number of patients considered for the trial but not invited to enter because their risk is deemed too high or within acceptable limits for surgery, along with the reason(s) for why they were not considered suitable.

**Table 1 Tab1:** Guidance for definition of higher risk from surgical complications

Group A		
Suitable for surgery—but at higher risk of complications compared to group B (potentially eligible for SABRTooth)	▪ CPEX—VO_2_ max 10–15 L/kg/min ▪ ISWT—walk 250–400 m ▪ Mortality risk from Nottingham score: 6–20 % at 90 days	The patient can be approached for the trial if they meet one or more of these criteria
Group B		
Suitable for surgery—lower risk of complications	▪ CPEX—VO_2_ max >15 L/kg/min, anaerobic threshold ▪ ISWT—walk >400 m and without significant desaturation ▪ Predicted post-operative FEV_1_ > 50 % ▪ Mortality risk from Nottingham score <6 % at 90 days for lobectomy (it is not anticipated that patients will need a pneumonectomy in this group of peripheral cancers).	Not suitable for the trial
Group C		
Unsuitable for surgery as predicted risk of complications is too high	▪ CPEX—VO_2_ max <10 L/kg/min ▪ ISWT—walk <250 m and significant desaturation ▪ Pre-operative FEV_1_ < 30 % ▪ Mortality risk from Nottingham score >20 % at 90 days for lobectomy (it is not anticipated that patients will need a pneumonectomy in this group of peripheral cancers). ▪ Reduced ejection fraction (e.g. <40 %) or evidence of ongoing myocardial ischemia ▪ Recent cerebrovascular event (e.g. within 3 months of planned surgery)	Not suitable for the trial

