### Sample size

As the study is designed to assess the feasibility of conducting a definitive large-scale phase III trial, a formal power calculation is not considered appropriate as effectiveness is not being evaluated.

For this feasibility study, we plan to recruit 54 patients in total (i.e. 27 to each treatment arm) from six UK hospitals, four tertiary treatment centres and two smaller referral units, over a 21-month recruitment period.

Achieving the recruitment targets within the feasibility study will help demonstrate that, when recruitment rates are scaled up, recruitment into a large-scale phase III trial is feasible. It has been estimated that 690 patients are required for the phase III trial to have 80 % power to show non-inferiority (NI) of SABR to surgery, where this is defined as SABR being less than 8 % worse in terms of 3-year OS (derived from an in-house simulation programme which accounts for the likely excess early death rate in the surgery arm in comparison with the SABR arm). This sample size also yields >97 % power for a similar 10 % NI margin for difference in mean quality-adjusted life years (QALYs) per arm and greater than 80 % power to show superiority.

In order to demonstrate the feasibility of recruitment within this feasibility study, we are aiming to recruit on average three patients per month from four UK large treatment centres and two smaller referral units. This equates to 36 patients per year (i.e. 9 patients from each of the 4 large treatment centres). Including these 4 established centres (and their referral units) within a subsequent phase III trial, recruiting at the same rate, 180 patients could be recruited over a 5-year period. We would also aim to include an additional 15 UK large treatment centres, plus their associated referral units. If these 15 centres recruited at 75 % of the rate of the centres within the feasibility study, an additional 100 patients could be recruited a year; 500 patients over a 5-year period. Thus, with approximately 19 large treatment centres and their associated referral units, a target of 690 patients over a 5-year period would be feasible, which equates to a rate of 138 patients per year.

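### By-arm complication rates are specified for related events, which rests on unblinded attribution; all collected complications should be tabulated, with the related subset alongside

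*Protocol article*

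**What the plan says.** Under Exploratory data analysis, the Protocol article fixes the complications output: "Rates of related complications, serious complications and unexpected serious compliances will be reported by treatment arm and overall". The word *compliances* is evidently a slip for *complications*. The sentence does not mention severity beyond the serious categories.

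The Follow-up section lists complications after surgery or SABR, with their severity, among the data collected. It attaches no condition that they be related to treatment. It also lists the MRC dyspnoea score, which is one of the pre-treatment assessments too.

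Trial design states that "it is not possible to blind patients or clinicians to treatment allocation". Trial population describes the target group as including "patients with poor lung function who are at risk of increased post-operative dyspnoea that would be sufficient to be unacceptable to them" and "patients who have an increased risk of cardiovascular morbidity that might lead to a perioperative complication or death".

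Statistical methods and analysis says that "the analysis will be performed through descriptive statistics rather than formal hypothesis testing". Its interim report to the trial steering committee covers expected serious complications and unexpected serious complications, and does not use the word *related* for either.

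**The concern.** Relatedness is a judgement. In an open-label trial with no stated masking of that judgement, whoever makes it can know the arm. In patients with poor lung function or cardiovascular risk, a respiratory or cardiac event may come from the treatment or from the existing disease, so the judgement is uncertain. Surgery and SABR differ in kind, and there is no reason to expect the same share of events to be called related after each. A by-arm rate of related complications then mixes two things: how often complications happen, and how often they are attributed.

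The article collects complications without a stated filter and brings one in at reporting. It also uses *related* in the final output but not in the interim list. At stake is how readable the descriptive complication table is. The table informs the trial team and will be seen by those designing a phase III trial. The feasibility conclusion is not at stake.

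**Working it through.** **1. The sections side by side.**

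| Section | What it covers | Relatedness filter stated? |
|---|---|---|
| Follow-up | Complications after surgery or SABR, with severity | No |
| Statistical methods and analysis (interim) | Expected serious and unexpected serious complications | No |
| Exploratory data analysis (complications) | Related complications, serious and unexpected serious complications, by arm | Yes, for at least the first item |
| Exploratory data analysis (mortality) | 30-, 90- and 180-day mortality by arm, 95 % CI | No |

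The complications sentence can be read in two ways. If *related* governs all three items, the final output filters the serious categories while the interim report does not. If it governs only the first, the filter affects the general complication count alone. The interim wording favours the second reading but does not settle it.

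**2. Whether any stated figure can be reproduced.** None can. The article gives no complication rate, attribution share or margin for harms. The only usable input is the sample size of 54 in total, 27 per arm (Sample size).

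**3. Illustration of the mechanism, on assumed values.** Let p be the true complication rate, equal in both arms, and let a be the share judged related in an arm.

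- Reported related rate in an arm = p × a
- Apparent difference = p × (a_surgery − a_SABR)
- 95 % half-width of a difference = 1.96 × √[r₁(1 − r₁)/27 + r₂(1 − r₂)/27], where r₁ and r₂ are the reported rates

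Worked case, p = 30 %, with 90 % and 50 % judged related:

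- Surgery: 0.30 × 0.90 = 27 % (27 × 0.27 = 7.3 patients)
- SABR: 0.30 × 0.50 = 15 % (27 × 0.15 = 4.1 patients)
- Apparent difference: 12 points, with a true difference of 0
- Half-width: 1.96 × √[(0.27 × 0.73 + 0.15 × 0.85)/27] = 1.96 × √(0.3246/27) = 21.5 points

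| Assumed true rate, both arms | 90 % v 90 % related | 90 % v 70 % related | 90 % v 50 % related |
|---|---|---|---|
| 20 % | 0 (half-width 20.5) | 4 (19.5) | 8 (18.4) |
| 30 % | 0 (23.7) | 6 (22.7) | 12 (21.5) |
| 40 % | 0 (25.6) | 8 (24.8) | 16 (23.6) |
| 50 % | 0 (26.5) | 10 (26.0) | 20 (24.9) |

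Entries are percentage points. Swapping the two attribution shares reverses the sign, so the illustration gives no direction. With equal attribution the difference is zero, as it would be in a table of all events.

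**4. What this shows.** Differing attribution alone could produce gaps of 4 to 20 points on these assumptions. Every one is smaller than its half-width (18 to 27 points), so at this sample size it could not be told from chance. Sampling error shrinks as numbers grow, whereas an attribution effect does not, so the habit is better not carried forward.

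**The case against.** The strongest objection is that this is a descriptive, exploratory output in a feasibility study. No test of complications between arms is planned, and the Sample size section says that "a formal power calculation is not considered appropriate as effectiveness is not being evaluated". That stands, and it limits the weight of the point.

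Second, *related* may govern only the first item, so a reader who infers that all harms are filtered goes beyond the text. This also stands. The sentence is ambiguous, and that is a reason to clarify it rather than to assume the worse reading.

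Third, complications described as following surgery or SABR may already mean treatment-linked events, with *related complications* merely a short name for them. A reader might infer that collected events are thrown away, but the article does not establish this. What remains is that the reporting sentence states a qualifier that the collection list does not.

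Fourth, who judges relatedness, and by what criteria, belongs to the full protocol or analysis plan. Agreed: no fault is found in that absence. The point concerns the output that the article does specify.

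Fifth, harm does not rest on attribution alone. Mortality at 30, 90 and 180 days and overall survival are reported without attribution wording. That stands.

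Sixth, MRC dyspnoea is recorded unblinded too. That is right: it avoids the relatedness judgement but is not free of open-label influence.

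**Conclusion.** The point holds as a modest one. The specified by-arm complication rates depend, at least for the general count, on an unblinded judgement of relatedness in patients whose co-morbidity makes that judgement uncertain. The judgement may differ between surgery and SABR.

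A reader might infer that the plan will make SABR look safer. The article does not support that: it gives no attribution shares, and it does not say that surgical events are more readily called related or that later events after SABR are put down to existing disease. Nor does it support treating complication rates as central to the phase III trial, whose stated aims are non-inferiority on survival, quality-adjusted life years, costs and quality of life. The 12-point example and the 4-to-20-point range rest wholly on assumed rates and lie within sampling uncertainty at 27 per arm. Mortality and the primary recruitment objective are unaffected.

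The change is still worth making, because it uses data already listed for collection and removes an avoidable source of difference between arms.

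**What to change.** Under Exploratory data analysis, reword the complications sentence so that:

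- all complications collected under Follow-up are reported by arm, overall and by severity, regardless of judged relatedness, with the related subset in an adjacent column;
- serious and unexpected serious complications are stated not to be filtered by relatedness, in line with the interim list under Statistical methods and analysis;
- *compliances* is corrected to *complications*;
- change in MRC dyspnoea score from baseline is summarised descriptively by arm, with a note that it is also recorded unblinded.

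The interim report needs no change beyond consistent wording.

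The cost is one reworded sentence, one wider table and one short summary, with no new data collection. The downside is that background events from co-morbidity will raise the rates in both arms; the adjacent related column keeps the narrower count visible.

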## Discussion

To know whether SABR is a better, equivalent or inferior alternative to surgery for higher risk patients is a key question in lung cancer. The primary aim of this feasibility study is to demonstrate that, over 21 months, enough patients can be randomised from 6 centres to indicate that a phase III trial recruiting 690 patients over 5 years in 20 UK centres would be feasible. The multiple secondary and exploratory endpoints will help determine the most optimum recruitment and data collection strategies and help optimise the design of a future phase III trial where the key aims would be to show NI of SABR to surgery and determine the relative costs of the two treatments and their effects on quality of life. Other studies comparing SABR to surgery have closed early due to poor recruitment, and therefore, the SABRTooth trial is a pragmatic study based on everyday practice in hospitals managing lung cancer. Considerable effort has been made to try and maximise recruitment.The SABRTooth feasibility study has been designed around the UK NHS cancer pathway for managing lung cancer.Neither histological proof nor exact quantitative measurement of risk for surgery is mandated for entry into the trial.The protocol has been developed through national lung cancer meetings over the past 3–4 years to promote awareness to the UK clinical oncologists, respiratory physicians and thoracic surgeons.A strong MDT with representatives of all concerned medical specialities involved in the management of lung cancer has developed the protocol.A small number of centres with highly motivated clinicians have been selected.PPI has been critical to the development of the protocol, lay summary and patient information leaflets.Mock patient interview scenarios with constructive feedback have been produced to provide a guide on how to approach and discuss the trial with patients.The trial is introduced to patients by a “neutral” respiratory physician and then, if the patient is interested in the study, consent is obtained by a lung cancer trials nurse.Approached patients who decline randomisation or their allocated treatment arm are offered an interview to explore their reasons for not entering the trial. Lessons learnt can then be used to try and improve recruitment.

Therefore, we believe that such a well-designed feasibility study in this clinical scenario will address very important issues of clinician and patient equipoise. We hope that, if this study is successful, we will be able to progress to a national randomised phase III study.

